## Abstract

**Background:**

People with dementia (PwD) experience a range of negative behavioral and psychological symptoms which can lower their quality of life. Because of the increasing prevalence of dementia, interventions that maintain and enhance the quality of life for PwD are needed. Listening to individualized music constitutes a promising non-pharmacological intervention for PwD. However, despite some preliminary results, evidence regarding the effectiveness of such interventions has been mixed and previous studies have shown a number of methodological limitations. In a randomized controlled trial, we address the limitations of previous research and assess the feasibility, efficacy, and acceptability of an individualized music intervention for PwD living in a nursing home.

**Methods:**

Residents with dementia from four to five nursing homes in Germany will be randomly assigned to either an intervention or control group. The intervention group will listen to personally-relevant music for 20 min every other day for six weeks. Nursing staff will assess participants’ quality of life and problem behavior at the six-week baseline, pretest, posttest, and at the six-week follow-up. Additionally, the participants’ behavior will be observed during the intervention period by project staff. The implementation, acceptance, and applicability of the intervention will also be evaluated.

**Discussion:**

The study results will show whether an individualized music intervention can improve the quality of life for PwD living in a nursing home. Additionally, it will provide valuable insight into the acceptability and implementation of an individualized music intervention in the institutional care setting. If the individualized music intervention proves to be effective and widely applicable, it could be implemented on a large scale in institutional care as an easy-to-administer intervention.

**Trial registration:**

German Clinical Trials Register DRKS00013793; ISRCTN registry, ISRCTN59052178, date applied 27 February 2018, date assigned 4 April 2018, retrospectively registered.

## Background

The increasing prevalence of dementia raises the question of how the quality of life and care for people with dementia (PwD) can be maintained and enhanced. PwD experience a range of negative behavioral and psychological symptoms such as agitation and depression [1, 2] which can lower not only their own quality of life but also that of their caregivers [3–5]. To avoid potential negative side-effects of pharmacological therapies [6–8], it is widely suggested that non-pharmacological interventions, which help create more satisfying living environments for PwD, are desirable [9, 10]. In this regard, PwD are thought to particularly benefit from individualized music interventions based on an individual’s own preferences and experiences.

Previous research shows that listening to personally meaningful music can facilitate positive social interactions [11] and promote positive emotions and memories as well as a reduction of stress, agitation, and anxiety in PwD [12–14]. The potential benefit of individualized music interventions for PwD is also discussed in the neuroscience literature, as dementia affects the specific brain areas (supplementary motor area) associated with long-term music memory functions to a lesser extent [15, 16]. Therefore, PwD continue to remember personally-relevant music very well. Moreover, listening to individualized music initiates a complex interaction between different brain regions which results in alertness, relaxation, interest, and a positive mood [17].

Thus, individualized music can be regarded as a promising non-pharmacological intervention for PwD to improve their quality of life. Quality of life is understood here as a superordinate construct which refers to an improvement of well-being and social participation as well as a reduction of depressive symptoms and problem behavior.

Preliminary evidence with regard to the effectiveness of individualized music interventions has been provided for the reduction of agitation and anxiety [18–20] as well as for increases in communication behavior, well-being, and the expression of positive emotions [21, 22]. Nevertheless, the amount of studies is limited and previous evaluations showed several methodological limitations, as most of them were quasi-experimental and pilot-trials including only small samples. Evidence about the effectiveness of music interventions in general (active and passive form) has been mixed [23]. In addition to the mostly poor methodological quality of studies which has been noted by systematic reviews and meta-analyses [23–28], interpreting the results of previous music intervention evaluations is difficult due to the diversity of intervention approaches (e.g. with regard to dosage). In particular, previous evaluations have seldom reported precisely how the intervention was implemented (e.g. how personally-relevant music was identified) or assessed implementation success.

In sum, although previous reviews and individual studies have provided some evidence that individualized music interventions can improve the quality of life for PwD, evidence regarding the effects of individualized music interventions for PwD is mixed and more methodologically rigorous studies are needed.

In the current study, we address the methodological limitations of previous studies by using a randomized controlled trial (RCT) with a large sample size, following a careful implementation procedure and evaluating the implementation success. The aim of our study is to assess the feasibility, efficacy, and acceptability of an individualized music intervention for PwD in institutional care. The primary objective is to evaluate whether the individualized music intervention improves the quality of life of PwD compared to standard care. Further objectives are to evaluate whether the individualized music intervention can be implemented successfully in the institutional care setting and to determine the level of acceptability in relation to the intervention.

We hypothesize an improvement of quality of life in participants in the intervention group (IG) compared to the control group (CG). In particular, the intervention is expected to enhance well-being, quality of sleep, and social participation as well as reduce depressive symptoms and problem behavior (i.e. agitation and resistance to care). In addition, we expect to observe positive short-term effects during and after the music listening sessions including emotional and motor changes (e.g. facial expression, body movement, and other positive reactions) as well as improvements in communication, attention, and orientation. We expect to find high levels of acceptability and that implementing the individualized music intervention in multiple nursing homes will be perceived as feasible.

## Methods

### Design

This study is a multi-center RCT with a baseline (T0; six weeks before treatment), pretest (T1), posttest (T2), and follow-up (T3; six weeks after treatment) design. The study will take place successively in four to five nursing homes in Thuringia, Germany. The participants will be randomly assigned to an intervention or a control group. Following T0, random allocation in a 1:1 ratio will be performed stratified by gender using a computer-generated randomization list for each nursing home. The randomization will be performed by a member of the study team not involved in the baseline assessment using the random number generator Random.org.

At four assessment points, the nursing staff will conduct external assessments (see trial flow diagram, Fig. 1). Additionally, the participants’ behavior will be observed during the intervention period.

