#### Problem behavior

To assess resistance to care via external assessment, a single item and visual analogue scale, based on Wilz and Soellner [29], will be used. In addition, agitated behavior will be assessed using the German version of the Cohen-Mansfield Agitation Inventory (CMAI; [31, 32]) which measures physically aggressive behaviors (PAB; e.g. hitting), physically non-aggressive behaviors (PNAB; e.g. general restlessness), and verbally agitated behaviors (VAB; e.g. repetitious sentences or questions) over the preceding two weeks. Each of the 29 items is rated on a seven-point scale of frequency. In addition, a five-point scale (from 1 = never to 5 = extremely) will be used for measuring disruptiveness of behavior. Cronbach’s *α* for the German version is .80 [32]. Furthermore, the German version of the Nurses Observation Scale for Geriatric Patients (NOSGER; [33]) will be used. It consists of six dimensions (memory, instrumental activities of daily living (IADL), basic activities of daily living (ADL), mood, social behavior, and disturbing behavior) with five items each. Each item is rated on a five-point scale of frequency of occurrence. The test-retest reliability for the six dimensions lies between .75 and .93.

In addition, goal attainment scaling (GAS; [34]) will be used to evaluate participants’ personal goal attainment. At T1 a member of the nursing staff will specify the participant’s personal goals for the individualized music intervention (IG) or for the standard offer of activities in the nursing home regarding the following six weeks (CG) in assistance by a member of the project team. At T2 nursing staff will rate participants’ personal goal attainment on a five-point scale, where point zero denotes the initial state being maintained or remaining stable. A lower value indicates a mild (− 1) or severe (− 2) deterioration from the certain goal, whereas positive scale values represent a positive change from the initial state in the sense of partial (+ 1) or complete (+ 2) goal attainment (cf. Chew et al. [35]).

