### Procedure

Six weeks before the intervention starts (T0), the severity of dementia will be assessed with the Mini-Mental State Examination (MMSE, [37]). At the same time, the nursing staff will conduct the first external assessments by completing different questionnaires regarding quality of life and problem behavior of PwD as described above. If the respective nursing staff member conducting the external assessment is uncertain about his or her assessment, a member of the project staff will attend the case conferences in the nursing home to obtain the missing information.

At T0, additionally relevant personal data of the participating PwD (e.g. medication, other physical and psychological diagnoses) will be assessed. As part of the assessments at T1, T2, and T3, any changes in personal data will be recorded. After completion of T0, participants will be randomly assigned to IG and CG.

Following randomization, the individualized playlists of the preferred music will be created for participants of the IG. We will gather information from family members, nursing home staff, and directly from participants if they are able to verbalize their personal preferences. A questionnaire developed by the project team (based on Gerdner [38], Gerdner and Schoenfelder [39], and a search of popular music from different decades) including a list of examples of popular artists and song titles will be used to identify personally-relevant music for each participant. Additionally, a telephone or face-to-face interview will be arranged with family members and/or participants themselves to get more detailed information about their music preferences. Based on this information, up to three individualized playlists for each participant will be compiled. Standardized documentation sheets will be used to record the characteristics of each playlist (number of playlist, number of tracks, duration of compilation).

Further external assessments by the nursing staff regarding quality of life and problem behavior will be conducted directly before (T1) and after the intervention (T2). At posttest, acceptance and applicability of the music intervention will be assessed. The follow-up assessment will take place six weeks after the end of the intervention (T3).

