### Data analysis

The data will be analyzed using SPSS (IBM Corp., Armonk, NY) and R (R Development Core Team, Vienna, Austria).

Descriptive statistics of playlist characteristics, number of music sessions, music session duration, the proportion of cancelled sessions, and why sessions were cancelled will be reported as indicators of implementation quality.

To check whether the randomization was successful, baseline characteristics and the pre-test levels of the outcome measures will be compared between IG and CG. Further analyses will be adjusted for any potential significant differences.

“As randomized” analyses will be performed retaining participants in the group to which they were originally allocated regardless of protocol adherence. In addition, per protocol analyses will be conducted based on the sample of participants who adequately adhered to the intervention protocol by completing at least five out of the 21 music listening sessions. Any differences between protocol non-adherers and protocol adherers as well as dropouts and those who complete the study will be analyzed regarding baseline characteristics and pre-test levels of the outcome measures.

Multilevel models for discontinuous change [41] will be performed for the primary outcomes to evaluate whether outcomes show different change patterns between IG and CG from baseline (T0) to pretest (T1) to posttest (T2) to follow-up (T3). Following Göllner et al. [42], three contrast variables will be computed by subtracting the baseline values from pretest (T1-T0), posttest (T2-T0) and follow-up values (T3-T0), respectively. The multilevel models will have two levels: the four assessments of the outcome variables as level-1 and participants as level-2. To examine average treatment effects, group membership will be included in the multilevel models as a dichotomous level-2 predictor (0 = CG, 1 = IG). Differential effectiveness will be analyzed by including the severity of dementia and its interaction term with the group membership variable as person-level moderator variables. Full maximum likelihood estimation will be used to account for missing data.

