## Discussion

This study will evaluate whether an individualized music intervention can be successfully implemented in the institutional care setting and improve the quality of life of PwD living in a nursing home.

The study has several strengths. To address the methodological limitations of previous studies, a RCT with a large sample of PwD living in multiple nursing homes is conducted. Our study also includes the systematic identification of personally-relevant music for each participant, the continuous examination and adaptation of playlists, and a higher dosage of individualized music listening sessions in comparison with the interventions evaluated in previous studies. We also address limitations of previous studies by following a careful implementation procedure and by evaluating the implementation success.

Another strength of this study is its robust design with four assessment points including a baseline, pretest, posttest, and follow-up assessment allowing the evaluation of different change patterns between IG and CG, as well as its long-term effects of the individualized music intervention. The study design also allows for controlling the progression of dementia. Additionally, the multiple, detailed and controlled observation of behavior constitutes an innovative novelty in the context of individualized music interventions. PwD with all severity stages will be included in the study.

However, there are also limitations identified in this study. First, nearly all outcomes will depend on the external assessment by the nursing staff. Nevertheless, the outcomes will be disease specific and, in our opinion, assessments by nursing staff will be most valid for this purpose. In addition, observation of behavior will be performed due to trained raters. Future research may also include physiological outcomes (e.g. cortisol, heart rate) as potential outcome measures.

Second, blinding is not possible in the design of the proposed study since the nursing home staff and project staff will accompany and monitor the participants during the intervention period and will, therefore, know which participants receive the music intervention and which do not.

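### T1 is rated after randomisation, probably by some staff who know the arm, yet it serves as the check on randomisation and can trigger adjustment

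*Protocol article*

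**What the plan says.** The Design section gives four assessments: "baseline (T0; six weeks before treatment), pretest (T1), posttest (T2), and follow-up (T3; six weeks after treatment"). Allocation comes straight after the first of them: "Following T0, random allocation in a 1:1 ratio will be performed". The Procedure section repeats this: "After completion of T0, participants will be randomly assigned to IG and CG".

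The next step concerns one arm only: "Following randomization, the individualized playlists of the preferred music will be created for participants of the IG". On the sources for these playlists, the Procedure section says: "We will gather information from family members, nursing home staff, and directly from participants if they are able to verbalize their personal preferences". It adds an interview, by telephone or in person, with relatives, residents or both. T1 is then rated directly before the first session. Nursing staff are the raters at all four time points (Design; Primary outcome measures).

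At T1 nursing staff have a second task, described under Problem behavior: "At T1 a member of the nursing staff will specify the participant’s personal goals for the individualized music intervention (IG"). For control residents (CG), the goals refer to the home's standard activities instead.

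Under Data analysis, the success of randomisation is to be judged as follows: "baseline characteristics and the pre-test levels of the outcome measures will be compared between IG and CG". Later analyses are then adjusted for any significant difference found. The three modelled contrasts are T1-T0, T2-T0 and T3-T0.

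The Discussion says that blinding is not possible, and gives as the reason that "the nursing home staff and project staff will accompany and monitor the participants during the intervention period".

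**The concern.** T1 looks like a second untreated baseline, and the plan uses it as one. But it falls after allocation, and two steps at or before T1 can tell nursing staff a resident's arm: the consultation about IG residents' music, and the setting of arm-specific goals. The reason given for not blinding does not cover T1, because no session has taken place by then. Any unblinding at T1 comes from the order of steps and not from the nature of the intervention.

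Three uses of T1 are exposed.

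- **The T1-T0 contrast.** It is meant to show change before any music session. A rating shift from knowing the arm would appear there as a difference between groups.
- **The randomisation check.** A difference at T1 cannot be attributed to chance imbalance if it could also arise from knowledge of the allocation.
- **The adjustment rule.** A significant T1 difference would make later analyses condition on a variable measured after randomisation. If that difference was itself produced by allocation, the adjustment can distort the treatment estimate instead of correcting it. T1 would also then be both an outcome and a covariate in the same set of analyses.

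Rater expectation is a realistic worry here. The Discussion concedes that nearly all outcomes depend on nursing staff assessment, and several are single items or visual analogue scales.

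**Working it through.** **Order of events**

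1. T0, six weeks before treatment: nursing staff ratings (Design, Procedure). No allocation exists yet.
2. Randomisation, after T0 (Design, Procedure).
3. Playlist work for the IG only, drawing on family, nursing home staff and residents (Procedure). No equivalent step is described for the CG.
4. T1, directly before the first session: nursing staff ratings (Procedure) and arm-specific goals set by a nursing staff member (Problem behavior).
5. Sessions, accompanied by project or nursing home staff (Intervention). The Discussion's reason for not blinding starts to apply here.

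Step 4 follows step 2, so T1 is post-randomisation. A goal for the music intervention cannot be written without knowing that the resident is in the IG, so at least one nursing staff member per resident knows the arm at T1.

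**Where T1 enters the analysis**

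| Element in Data analysis | Uses T1? |
|---|---|
| T1-T0 contrast | Yes |
| T2-T0 and T3-T0 contrasts | No, the reference is T0 |
| Comparison of pretest levels as the randomisation check | Yes |
| Adjustment for significant differences | Yes, if the difference is at T1 |

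**Illustration of size**

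The article gives no figure for rater expectation, so a shift δ of 0.1 to 0.2 SD is assumed. From the Sample size section, 130 recruited at 1:1 gives 130/2 = 65 per arm. A two-sided test at .05 is taken, with the normal approximation.

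Standard error of a level difference at T1, in SD units: √(2/65) = 0.175.

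Chance of significance: Φ(−1.96 + δ/SE) + Φ(−1.96 − δ/SE).

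- δ = 0: 0.025 + 0.025 = 5%.
- δ = 0.1: δ/SE = 0.57, so 0.082 + 0.006 = 0.088, about 9%.
- δ = 0.2: δ/SE = 1.14, so 0.206 + 0.001 = 0.207, about 21%.

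With only the 92 participants that the article says are needed (46 per arm), SE = √(2/46) = 0.209 and the figures are about 8% and 16%.

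For the T1-T0 change, a T0-T1 correlation is also needed. Take .75 as an assumption, the lower end of the NOSGER retest range under Problem behavior. The variance of a change is 2(1 − .75) = 0.5, and with 65 per arm SE = √(2 × 0.5/65) = 0.124. The chances are then about 13% (δ = 0.1) and 36% (δ = 0.2). They would be higher with a higher correlation.

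All of these are per outcome, and several outcomes are compared.

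**The case against.** The strongest reply is that the main treatment contrasts are safe. T2-T0 and T3-T0 start from T0, which was rated before anyone could know the arm. This stands. A reader might infer that the trial's main effect estimates are compromised; the document does not support that, except through the adjustment rule.

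A reader might also infer that every T1 rater is unblinded. The text does not say so. It never states when raters are told the arm. It does not say that the staff member who supplies playlist information or writes the goals is the one who rates, and it does not fix the order of goals and questionnaires within T1. An article may leave such detail to the full protocol. Knowledge of the arm among some raters is therefore a fair inference and no more. But nothing in the text protects T1 either.

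A third tempting reading is that the music interviews are already treatment and change residents' behaviour by T1. That is conjecture. The Intervention section defines the intervention as the listening sessions, and the interview may be by telephone and with relatives alone.

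A reader might want the assumed shift expressed as a share of the planned effect. No such ratio is given here, because reading f = 0.2 as a plain two-group difference of 0.4 SD requires about 326 participants, not the stated 92.

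Two practical points also stand. Asking about music only in the IG spares CG families and avoids prompting music use in the CG. And if T1 is blinded while T2 is not, any expectation shift falls wholly between T1 and T2. No planned contrast runs from T1 to T2, so this affects only informal readings of that interval.

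Finally, lack of blinding is already disclosed as a limitation. The disclosure is general, though, and its stated reason does not extend to the pretest.

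**Conclusion.** The point holds in a limited form. T1 is measured after randomisation, probably by some raters who know the arm, and the stated reason for not blinding does not apply to it. That T1 is post-randomisation is explicit in the article; that some raters know the arm is inferred from the playlist consultation and the arm-specific goals.

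The harm is confined to the T1-T0 contrast, to T1 levels as proof of successful randomisation, and to adjustment triggered by a T1 difference. T0 stays clean as a reference for T2 and T3.

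The size is unknown. The 9-21% is an illustration that rests on an assumed 0.1 to 0.2 SD shift and 65 per arm; the document offers no evidence for or against a shift of that size. The change should be made because it is cheap and removes an avoidable ambiguity, not because a large bias has been shown.

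**What to change.** 1. At T1, have nursing staff complete and return the outcome questionnaires before they are told a resident's arm. Set the GAS goals only afterwards, before the first session.
2. Ask nursing staff, and families by questionnaire sheet, for the music preferences of all participants at T0. Compile playlists for the IG only. Where feasible, hold the IG interviews after the T1 ratings; otherwise acknowledge that contact as a remaining limitation.
3. Base the randomisation check and any adjustment on T0 values only.
4. In the Discussion, limit the statement that blinding is not possible to T2, T3 and the behavioural observations.

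**Cost.** About 65 extra short sheets for the CG, and a reordering of steps with the allocation held within the project team until T1 is returned. Holding interviews after T1 shortens the time for compiling playlists. Asking about CG residents' music might prompt some music use in that arm. Blinding at T1 will be imperfect if a relative or resident mentions an interview. No extra assessments or participants are needed. Items 3 and 4 are changes of text only. Because the homes enter successively, items 1 and 2 could still be applied in homes that have not yet reached T0.
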